## **Risks to the Subjects**

Human Subjects Involvement and Characteristics. This project will screen approximately 250 postmenopausal female subjects, 50-65, in relatively good physical health who either, at risk for cognitive decline (personal or family history of mood disorder, hypothyroidism, family history of AD, APOE- $\epsilon 4$  allele). Exclusion criteria include: a) diagnosis of possible or probable AD, or any other dementia (e.g., vascular, Lewy body, frontotemporal), b) evidence of neurologic or other physical illness that could produce cognitive deterioration. Volunteers with a history of TIAs, carotid bruits, or lacunes on MRI scan will be excluded. During physical and neurological examination, subjects will be screened for Parkinson disease using the motor examination (items 18-31) of the Unified Parkinson's Disease Rating Scale, an instrument with high inter-observer concordance, to quantify presence and degree of symptoms, c) history of myocardial infarction within the previous year or unstable cardiac disease, d) significant cerebrovascular disease, as evidenced by neurological examination, uncontrolled hypertension (systolic BP > 170 or diastolic BP > 100), history of significant liver disease, clinically significant pulmonary disease, diabetes, or cancer, e) use of any of the following drugs will also exclude subjects: centrally active beta-blockers, narcotics, clonidine, anti-Parkinsonian medications, antipsychotics, benzodiazepines, systemic corticosteroids, medications with significant cholinergic or anticholinergic effects, anti-convulsants, warfarin, or sporadic use of phytoestrogen-containing products, f) evidence of depression as determined by a HAMD score of 8 or more (17-item version), g) history of drug or alcohol abuse, h) contraindication for MRI scan (e.g., metal in body, claustrophobia), i) current episode of mental illness (including mood disorders), or past history of mental illness (excluding mood disorders), j) cognitive decline, as evidenced by change in daily functions and/or MMSE <24.

Subject involvement will consist of: a) screening and identification of subjects who meet inclusion criteria; b) clinical evaluation (structured psychiatric interview, physical/neurological examination) and blood drawing for general chemistry and other analyses; c) baseline neuroimaging (MRI, PET) and neuropsychological assessments; and d) follow-up assessments over 2 years. Contact with subjects in-between visits will include telephone contact at least every other month. At each three-month interval subjects will be asked to return for a follow-up visit to evaluate their general well-being, overall functioning, and subjective memory performance. Subjects will also be encouraged to contact the research team as needed.

Sources of research material. Existing medical records will be used to determine eligibility of subject for study entry. In addition, the following materials will be gathered specifically for research purposes: blood samples for screening purposes and to monitor compliance, subjects' responses to rating scales and questionnaires, and PET and MRI scan data. Most subject data will come from four primary sources. First, face to face semi-structured interviews that will cover several aspects of medical, psychiatric and cognitive functioning. These instruments are described in the Research Design and Methods section of the proposal. These instruments have previously been used and validated and present no foreseeable risk to the subjects other than the inconvenience of the time it takes to administer them. The second primary source of

data is physical/neurological examination, as described in the Research Design and Methods. The third primary sources of data are laboratory assessments of blood. Finally, the fourth primary source of data is neuroimaging (PET, MRI). While human subjects will be studied at Stanford University, the key that links the unique subject number to subject identifiers will be maintained at Stanford only (where the P.I., [name], is located). Each subject studied at Stanford will be assigned a unique subject number. This number will not contain the subjects name, initials, date of birth, hospital ID number, or any other information that might be used to directly or indirectly identify the subjects. [name] at the UCLA site will not hold or have access to the key identifying the study subjects, nor will he directly interact with the study subjects; he will be involved strictly at the level of data analysis, as described above.

Potential Risks. The procedures involve minimal potential risks. Blood drawing, though a routine part of general medical examinations, entails a small possibility of such discomforts as bleeding, bruising, lightheadedness, fainting, or rarely, infection. Neuropsychological testing may induce feelings of failure, frustration, or anxiety. However, our psychometrist is experienced in assessing persons with memory impairment and conveys a relaxed and confident attitude. A minority of subjects experience anxiety and claustrophobia during MRI scanning. Potential drug (e.g. estrogen) side effects are monitored closely; medications are discontinued as indicated medically and appropriate interventions provided. The PET scan exposes subject to a small amount of radiation. The radiation dose the subjects receive is well within the accepted limits of the Nuclear Regulatory Commission for radiation workers.

### **Adequacy of Protection Against Risks**

Recruitment and Informed Consent. Currently, the PI is working as an Associate Professor and as the Associate Director of the Women's Wellness Program in the Department of Psychiatry and Behavioral Sciences at the Stanford University School of Medicine. The PI has had a longstanding interest in the interaction between reproductive hormones and brain function, and she was a physician in the WHIMS study at UCLA. In her new capacity, the PI will have access to the resources of the Women's Wellness Clinic, and there is strong enthusiasm from all collaborators at Stanford to work on this project.

One of the PI's primary responsibilities within the University is collaboration with the Center for Research on Women's Health and Reproductive Medicine at Stanford. The Center, with [name] as Director, provides the infrastructure for basic, clinical, and translational research grants and contracts in women's health. In addition, [name] and [name] (the PI for WHI study here at Stanford) will be at the core of the recruitment process. This collaboration will allow for the recruitment of subjects from the PREMPRO arm of the WHI study based here at Stanford University.

The main source of recruitment will be Stanford University Gynecology (Gyn) Division and Clinic. Clinic is on the third floor of the Stanford University Clinics in the Boswell Building, occupying 4,000 sq. ft. Immediately adjacent to the Clinic is the Center for Research on Women's Health and Reproductive Medicine. In the Center are the Clinical Coordinators and support staff for all clinical studies in the Center. There are two conference rooms in the Clinic where patients may be screened, protocols reviewed, and informed consent obtained. The GYN Clinic sees approximately 1,000 new patients per month. More than 45% of them are between

the ages of 45 and 70. Of these women, approximately 52% of perimenopausal women are currently taking estrogen, and 22% of postmenopausal women are taking estrogen. About 47% of the women taking estrogen are deciding to discontinue. Additionally, several local primary care clinics refer women for potential inclusion into research studies. Additional resources include: 39 families of AD probands from the Alzheimer Disease Family Study; a research team that has continued rapport with these families and is experienced in performing the proposed examinations; the multi-campus geriatric psychiatry and neurology group; Stanford University, Alzheimer's Disease Center and Stanford University VAMC. If a woman shows interest in the study, the study clinician and/or one of the investigators will meet with the woman to describe the study. All interviewing and testing procedures will be explained to the potential subject in detail. The research assistant will document consent by asking the subject a series of questions to verify comprehension of study procedures, risks and benefits. Consent will then be obtained.

Protection Against Risk. Subjects will be assured that they do not need to answer any question on the psychiatric, or cognitive function scales that they do not wish to address. Concerning the venipuncture, the minimum amount of blood necessary for analysis will be obtained.

Potential Benefits of the Proposed Research to the Subjects and Others. Potential benefits for subjects include the complete diagnostic assessment, which may identify underlying medical disorders so that appropriate referrals for treatment can be made. Subjects often express great satisfaction from knowing they have been able to make a personal contribution to the advancement of scientific knowledge and to the search for solutions to health problems – either their own or others'. For society, the increased understanding gained through this study may provide significant leads for treatment and prevention of AD, thus benefiting many older persons. The benefits, then, clearly outweigh the risks.

Because the procedures are time-consuming and subjects do not necessarily receive direct clinical benefits from them, subjects will receive a \$25 honorarium per visit and \$25/hour (total of \$100) for each MRI/PET scan, which also helps cover their travel costs.

The proposed research will help to define guidelines for estrogen use among postmenopausal women. Specifically, it will provide information regarding the effects of discontinuation from estrogen use on cognitive functioning.

Importance of the Knowledge to be Gained. There is little risk to participating in a study assessing the effects of continuation/discontinuation of estrogen use. Yet there is much to gain from identifying changes in brain metabolism and cognitive function, which may result from discontinuation of estrogen use.

- a) Individual: Subjects will receive a detailed psychiatric, physical, and neurological examination, including laboratory and cognitive assessment, and neuroimaging.
- b) Societal: Results of the study may further understanding of the possible protective effects of estrogen from cognitive decline.

## **Gender and Minority Inclusion**

Inclusion of Women and Minorities. Women are the subjects under investigation and there are no inclusion/exclusion criteria related to minority status. The study population will in part be

drawn from women's health clinics at Stanford and the surrounding community.

Inclusion of Children. As the research questions investigated in this project are specific to postmenopausal women, children will be excluded from the study.

Other Human Subjects Considerations. The characteristics of the proposed study populations are described in the inclusion and exclusion, evaluation, and research procedure portions of the Research Design and Methods section. The PI will routinely spend time to address any questions about the study and provide counseling and general information about cognitive decline and related issues.

Subjects are informed that information on individual genotypes is not provided to them because investigators are blinded to individual results and the analyses are not performed in a licensed clinical laboratory. Subjects who wish information on their genotypes are discouraged from obtaining such results if they do not have dementia, since APOE is not considered a predictive test and the potential psychological consequences of such information could be problematic [15]. Subjects who insist on such information are referred to the Clinical Genetics Division at Stanford University for counseling and further testing from a licensed clinical laboratory as indicated.

Only a small proportion of subjects is expected to develop cognitive decline during the study period. Thus, one concern is that some subjects are being exposed to potential side effects of randomization (in case of continued use, breast cancer risk; for those who discontinue, osteoporosis, etc.) for a condition that they will not develop. However, of the subjects who do not develop cognitive decline during the two-year follow-up period, a significant proportion is at risk for it and eventual AD in future years. Estrogen use if shown to be neuroprotective, may have beneficial effects for them as suggested by epidemiological studies that show estrogen use decreases risk for development of AD dementing process and brain metabolic alterations which begin years prior to clinical confirmation of the disease.

The responsibility for medical, psychiatric, and psychological care of subjects will remain with the subject's primary physician. The PI checks results of laboratory tests soon after they are received. Should abnormal findings be discovered at any time during participation in the project, the participant, and the responsible physician and, if appropriate, responsible relative is informed. Should the participant not have a physician, a referral is made to one in the patient's geographic area. With the subject's consent, copies of laboratory results are sent to their physician.

In conjunction with the Stanford University Human Subjects Protection Committee, all legal and ethical safeguards for participants are implemented. All participants receive a copy of the Subject's Bill of Rights prior to giving consent to participate. The informed consent form is read with each participant, allowing time for questions following each paragraph. Thus, the procedures, potential risks and benefits, right to withdraw and confidentiality are presented in a thorough and uniform manner to all participants.

Data and Safety Monitoring. Adverse events will be evaluated at each study visit and reported regardless of randomization outcome. Any event not previously documented in the study will be

recorded, including the nature of the individual experience, date and onset time, duration, severity, and potential relationship to intervention. Any changes in general well-being, corrective treatment or prescription of concomitant medication/s also will be recorded. Previously recorded adverse events will be reviewed at each visit. We will use nonspecific solicitation of adverse events by asking "Do you feel different in any way since starting the discontinuation of estrogen use?"

Adverse event severity will be rated as mild (noticed discomfort but no disruption of daily activity), moderate (discomfort affects daily activity), or severe (inability to perform daily activity). All adverse events will be followed, and any serious adverse event (e.g., life threatening, incapacitating) will be reported to the health authorities, including NIH, local IRB, and the GCRC Office of Research Participant Advocacy (ORPA). An external advisory group comprised from the national experts in the field of reproductive neuroendocrinology and neuroimaging (Drs. [name] and [name]) will review cognitive and brain imaging data blinded to the intervention every 6 months. Subjects in either arm who will exhibit worsened performance on cognitive tests will have an immediate work-up done, including neuroimaging (PET/MRI) done to evaluate potential changes in brain function and will be removed from the study.

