### **Subject Participation**

In the present study, participants will be randomly assigned to continue or discontinue their existing estrogen hormone therapy (HT) for the duration of the 2-year study. The assessment schedule includes: a) screening and identification of subjects who meet inclusion criteria; b) clinical evaluation and blood drawing for general chemistry and other analyses; c) baseline neuroimaging (MRI, PET) and neuropsychological assessments; d) interim assessments; and e) two-year follow-up assessments. All tests performed at baseline will be repeated at a 2-year follow-up. Interim assessments with subjects in between in-person visits will include telephone contact at least every other month. At each three-month interval subjects will be asked to return for a follow-up visit to evaluate their general well-being, overall functioning, and subjective memory performance. Subjects will also be encouraged to contact the research team as needed.

Psychiatric examination. The baseline psychiatric assessment includes a psychosocial history, Structured Clinical Interview for DSM-IV--Patient Edition (SCID), and mental status examination,

and will take approximately hours to complete. [name] will oversee the clinicians that perform the psychiatric assessments and evaluate interrater reliability.

The following standardized rating scales and questionnaire will be used:

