Neuropsychological assessment. The neuropsychological test battery includes two components: (1) baseline memory tests; (2) and follow-up measures to assess cognitive decline. The baseline battery includes measures that we expect to be sensitive to subtle changes in cognitive function as well as instruments that appear to have some value in prospectively identifying individuals who eventually decline and develop dementia. These tests are included under the assumption that cognitive changes may emerge in the same functional areas that are affected in the earliest stages of clinically detectable AD. The tests will be given during afternoon sessions to avoid diurnal effects. The neuropsychological test battery will include measures of secondary memory, retrieval from semantic memory/language, visuospatial ability, and frontal functions. The tests were chosen based on prior studies that indicate their ability to predict cognitive decline [9] and sensitivity to predict cognitive change [10]. Tests in the battery will include the Auditory Consonant Trigrams (ACT), Benton Visual Retention Test (BVRT), Boston Naming Test (BNT), Color Trail Making Test (Color Trails 1 & 2), Delis Kaplan Executive Function System (DKEFS) - Color-Word, and Verbal fluency subtests, Rey-Osterrieth Complex Figure Test (RCFT), Wechsler Adult Intelligence Scale-3rd Edition (WAIS-III) - Digit Span, Digit Symbol Coding, and Letter Number Sequencing subtests, and the Wechsler Memory Scale-III (WMS)-Logical Memory I & II subtests. Two subtests from the Wechsler Abbreviated Scale of Intelligence (Vocabulary and Matrix Reasoning) were used to characterize intelligence (IQ).

Laboratory Assessment. Laboratory studies are required to identify treatable medical illness that may cause cognitive impairment. We will use the laboratory screening recommended by

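### The scripted adverse-event question fits only the discontinuation arm, and the 6-monthly cognitive and imaging review has no scheduled interim test or scan behind it

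*Protocol*

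**What the plan says.** **Adverse events.** The Data and Safety Monitoring text (Protocol, under Gender and Minority Inclusion) states: "Adverse events will be evaluated at each study visit and reported regardless of randomization outcome". It describes the solicitation as nonspecific and gives one question: "Do you feel different in any way since starting the discontinuation of estrogen use". No other wording is given for women assigned to continue. New events, changes in well-being, treatments and concomitant medication are also recorded. Events are graded and followed, and serious ones go to the authorities.

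**External review.** The same text says an advisory group "will review cognitive and brain imaging data blinded to the intervention every 6 months". Women in either arm whose cognitive test performance worsens are to have an immediate work-up, including PET/MRI, and leave the study.

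**Assessment schedule.** Subject Participation lists "baseline neuroimaging (MRI, PET) and neuropsychological assessments" and then says: "All tests performed at baseline will be repeated at a 2-year follow-up". Between those points there is telephone contact at least every other month, and every three months women are asked "to return for a follow-up visit to evaluate their general well-being, overall functioning, and subjective memory performance". The Neuropsychological assessment paragraph gives the battery a second component, "follow-up measures to assess cognitive decline", without saying when it is given. In the Psychiatric examination text the depression scale (HAM-D) is 6-monthly, while the MMSE and the Clinical Global Impression scale have no follow-up times.

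**The concern.** There are two separate faults.

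First, the trial compares continuing with stopping estrogen, and the question presupposes stopping. A continuer has no valid answer to it. A discontinuer is told in the question what to attribute her symptoms to, which is not nonspecific solicitation. Subjective symptoms are the kind of event most affected by how one asks, so the two arms could report at different rates for reasons unrelated to treatment. This cannot be repaired after the data are collected.

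Second, the protocol relies on a 6-monthly look at cognitive and imaging data, and on a trigger that fires on cognitive test decline. On the stated schedule, neither has a scheduled post-baseline measurement to work with until a woman reaches 2 years.

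**Working it through.** **Step 1: the question against the arms.** Subject Participation randomises women to continue or discontinue their existing therapy. The monitoring text covers both arms at every visit. The scripted question refers to an act that only one arm performs. The three statements cannot all be followed as written.

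**Step 2: how many women.** Subject Recruitment expects about 71 randomised and 30% attrition. The plan's own figure reproduces: 71 × 0.70 = 49.7, against 50 to be retained. The allocation ratio is not stated.
- Assuming 1:1: 71 / 2 = 35.5 women in the continuation arm.
- If allocation were 2:1 in either direction: 71 / 3 = 23.7, or 71 × 2/3 = 47.3.
- Three-monthly visits over 2 years: 24 / 3 = 8 per woman who completes.

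**Step 3: what a 6-monthly review has for one woman.**

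| Measure | Stated timing | New data at months 6, 12, 18? |
|---|---|---|
| PET, MRI | baseline, 2 years | none scheduled |
| Neuropsychological battery | baseline, 2 years | none scheduled |
| Follow-up measures of decline | not given | cannot be told |
| MMSE, Clinical Global Impression | no follow-up time | cannot be told |
| Subjective memory, functioning, well-being | 3-monthly | yes, but neither an objective test nor a scan |
| HAM-D | 6-monthly | yes, but a depression scale |

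The unscheduled PET/MRI in the monitoring text does not fill the gap, because it follows cognitive worsening that some test must already have shown.

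**Step 4: what the reviews have across the trial.** Assume even accrual of 71 women over 36 months (the three recruitment years), 24 months of follow-up and 30% attrition. For month m from 24 to 60, the number of women with a baseline and 2-year pair is 71 × 0.70 × (m − 24) / 36; before month 24 it is zero.

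| Review month | Women with a pair |
|---|---|
| 6, 12, 18, 24 | 0 |
| 30 | 8.3 |
| 36 | 16.6 |
| 42 | 24.8 |
| 48 | 33.1 |
| 54 | 41.4 |
| 60 | 49.7 |

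So 4 of 10 reviews have baseline data only. The later ones have pairs only from women who have already completed their 2 years.

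**The case against.** **Other recording continues.** The scripted question is one prompt among several routes, and events are recorded, graded and followed in both arms. This stands. A reader might infer that the arms' adverse events cannot be compared at all. The protocol does not support that: a comparison is possible, with a risk of bias mainly in solicited subjective symptoms. Nor does it support a claim that breast cancer, which the protocol names as a risk of continued use, would be under-reported. A diagnosis or its treatment would be recorded whatever the prompt.

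**No blind is broken.** Women stop or continue their own therapy and no placebo is described, so they know their arm. This also stands. The fault is unequal prompting, not unblinding.

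**The protocol never says scans and tests happen only twice.** True. It lists interim assessments, leaves the follow-up cognitive measures and the MMSE untimed, and allows unscheduled imaging. The supportable statement is that baseline and 2 years are the only stated times. It does not follow that every interim review must be empty, and staggered entry gives some pairs from about month 30.

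**A failed promise to participants.** A reader might go further and say that a safeguard promised to participants does not work. The consent pages are not shown, and 3-monthly visits, telephone contact and serious-event reporting operate throughout.

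**The group's remit.** Not listing adverse events among the data for the advisory group contradicts nothing. Sending them there is a preference about monitoring structure.

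**Conclusion.** Both faults hold, within limits.

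The question is wrong as written. It does not apply to continuers and it cues discontinuers, so solicited subjective events may be ascertained differently by arm. It misfits about 35 of 71 women under an assumed 1:1 allocation (about 24 to 47 if allocation were 2:1 either way). The size of any bias cannot be computed from the protocol.

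The monitoring text and the assessment schedule do not match. No scheduled cognitive test or scan is stated for months 6, 12 or 18 of any woman's follow-up, and under even accrual the first four reviews have essentially no pairs. Whether untimed measures were meant to fill the gap cannot be told.

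The main PET analysis is not affected by the question's wording, and the Data Analysis section plans no between-arm test of adverse events. This should be corrected, but it does not undermine the trial's main comparison.

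**What to change.** 1. Replace the scripted question with one arm-neutral wording used identically in both arms, for example: *Have you noticed any change in your health since your last visit?* This changes one line in the protocol and on the visit form.

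2. Reconcile Subject Participation, the Neuropsychological assessment paragraph and the monitoring text. State when the follow-up cognitive measures and the MMSE are given, and make the 6-monthly review and the worsening trigger refer to data actually collected. If both are aligned to what is already scheduled, the cost is text only. If interim cognitive data were intended, repeat testing may be needed, at a cost in participant and staff time. What the trigger and removal rule should be is for the investigators; the point is only that the rule and the schedule must agree.

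3. Optionally, tabulate the adverse-event and HAM-D data by coded arm for the same advisory group. Review by coded arm is compatible with its blinding and uses data already collected.
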